## For the quantitative parameters, the descriptive statistics will be mean with standard deviation or median with range of minimum and maximum, and number of valid observations. Mean and median will be reported to a precision of one decimal place more than the individual measurements; standard deviation will be reported to a precision of two decimal places more than the individual measurements; and range will have the same precision as the individual measurements.

## For qualitative parameters (categorical or ordered), frequency counts and percentages of each category will be calculated by treatment group. Percentages will be reported up to 1 decimal place.

## Primary study parameter(s)

The primary null hypothesis for this study is that there is no significant difference in the mean change in the percent of total weight loss (%TWL) at five years, between patients treated with a TSBL adjusted BP limb length (active group) versus patients treated with a standard BP limb length of 150 cm (control group).

In addition to the descriptive statistics (see the above section : Patient demographics other baseline characteristics), the two treatment strategy groups will be compared using two-sample T-test if parameter is normally distributed. Visual inspection of the distribution, as well as the Shapiro-Wilk test for normality, will used to assess normality. Unless equality of variance between groups is established, the Satterthwaite method for t-statistics and 95% confidence intervals will be used. If data is skewedly distributed, a Mann-Whitney U-test (Wilcoxon two-sample test) will be applied. For the difference in medians, the Hodges-Lehmann estimate will be used with distribution-free 95% confidence intervals.

In addition to the above mentioned analyses, the homogeneity of treatment effect over different strata of patients will be evaluated. In this, differences in treatment effect over separate strata of potentially relevant factors (e.g. gender, baseline BMI, co-morbidities, compliance, etc) will be evaluated. A multivariable model will be used to formally establish homogeneity, i.e. the absence of effect modification for the potentially relevant factors, separately.

## Secondary study parameter(s)

All secondary endpoint parameters (quantitative and qualitative) will be presented as described in section : Patient demographics other baseline characteristics.

For the evaluation of differences between groups, the primary analysis approach will be applied for the quantitative secondairy endpoint parameters..

For the qualitative parameters a Fisher exact test or a Chi-square test will be used.

For the parameters related to the occurrence of side effects, the evaluation focusses on the “absence” of differences. For these analysis estimates of risk differences with 90% confidence intervals, based on the Farrington-Manning Method will be used (non-inferiority setting, one sided approach). Due to sample size constraints, formal hypothesis tests on non-inferiority will not be performed. Multivariable logistic (or log-binomial) regression modelling is not foreseen.

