12) To compare the proportion of patients between the groups at 1, 2, 3, 4 and 5 years with remission of hypertension, defined as a blood pressure of 140/90 mmHg or less without antihypertensive medication ^#^.

13) To compare the proportion of patients between the groups at 1, 2, 3, 4 and 5 years with improvement of hypertension, defined as a lower blood pressure of at least 10 mm Hg systolic and/or 5 mmHg diastolic, and/or less antihypertensive medication (not reaching the criterion of remission) ^#^.

14) To compare the proportion of patients between the groups at 1, 2, 3, 4 and 5 years with resolution of sleep apnea, defined by cessation of CPAP or other devices use, documented by their own pulmonologist

15) To perform analysis of the above parameters in the subgroups with TSBL 500-700 and >700.

16) To compare within the standard group of patients with an allocated BP-limb length of 150 cm those with a TSBL < 500 to those with a TSBL 500-700 and to those with TSBL >700 cm on the above mentioned parameters.

^#^ : patients are asked to bring along with their visit an overview of current medication from their local pharmacist and actual use will be checked with the patient. In case of absence of the overview, after informed consent is given, the local pharmacist will be asked to provide the investigator with an overview of the medication

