# METHODS

## Study parameters/endpoints

### Main study parameter/endpoint

Percent total weight loss (%TWL) at 5 years.

Assumptions : Control group : TWL of 35% (SD 12%)

Experimental group : TWL of 40% (SD 12 or 9%)

(Absolute difference TWL 5% with possible smaller SD)

Definition : TWL = ([initial weight – attained weight]/ initial weight) * 100

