### Secondary study parameters/endpoints

1) Percent of total weight loss (%TWL) at 1,2,3,and 4 years.

2) Percent excess weight loss (%EWL) at 1,2,3, 4 and 5 years.

Definition: %EWL (Initial Weight – Postop Weight) / (Initial Weight – Ideal Weight)

(ideal weight is defined by the weight corresponding to a BMI of 25 kg/m2 )

3) Percent excess BMI loss (%EBMIL) at 1,2,3, 4 and 5 years.

Definition: %EBMIL (ΔBMI / (Initial BMI – 25)) * 100]

4) Proportion of patients with 22 ≤ BMI ≤ 30 Kg/m^2^ at 1,2,3, 4 and 5 years

5) Mean number of daily bowel movements in the last two weeks at 6 months, 1,2,3, 4 and 5 years.

6) Mean number of days with daily bowel movements > 3 in the last two weeks at 6 months, 1,2,3, 4 and 5 years.

6) Quality of life measured by the RAND-36 questionnaire at 6 months, 1,2,3, 4 and 5 years, absolute and compared to before surgery.

7) percentage of patients experiencing moderate to severe dumping symptoms defined by the Dumping Severity Score (DSS) at 6 months, 1,2,3, 4 and 5 years, absolute and compared to before surgery.

Moderate to severe is defined as 3 or more dumping symptoms with a severity score of 2 or 3 on a 4-point Likert scale. Symptoms are divided in two categories, e.g. early and late,

as described by Emous et.al. (7)

8) percentage of patients who have neither deficiencies of iron, nor vit. D, nor vit B12 without extra suppletion, at 6 months, 1,2,3, 4 and 5 years . Deficiencies are based on the local normal laboratory values.

9) Proportion of patients who have a deficiency at 6 months, 1,2,3, 4 and 5 years, or received extra suppletion for:

- iron (ferritin)

- vitamin B_12_

- vitamin D_3_

- Vitamin B_1_

- Vitamin B_6_

- Folic acid

- Vitamin A

- Vitamin D

- Calcium

- Phosphate

- Albumin

- Zinc

- Copper at 1,3 or 5 years

- Selenium at 1,3 or 5 years

10)Proportion of patients at 1,2,3, 4 and 5 years without diabetes, both with remission and without de novo, defined as an HbA1c less than 48 mmol/mol without diabetes medication in the last 6 months.

11)Proportion of patients at one year and two years with improvement of diabetes, defined as a reduction of HbA1c of 10mmol/mol or more but not reaching remission criteria and/or less anti-diabetic medication.

12)Proportion of patients at 1,2,3, 4 and 5 years with remission of hypertension, defined as a blood pressure of 140/90 mmHg or less without antihypertensive medication.

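### The BMI 22–30 endpoint is compared only by a pooled test, which can hide opposite effects at low and high entry BMI

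*Protocol*

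**What the plan says.** Protocol section 7.1.2, item 4, lists "Proportion of patients with 22 ≤ BMI ≤ 30" kg/m² at years 1 to 5. The summary places it directly after the primary endpoint. For all binary secondary endpoints, section 9.2 states: "For the qualitative parameters a Fisher exact test or a Chi-square test will be used". The last sentence of that section is "Multivariable logistic (or log-binomial) regression modelling is not foreseen". It follows the text on side effects, Farrington-Manning intervals and non-inferiority.

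Baseline BMI does appear as a possible effect modifier in section 9.1, under the primary endpoint: "differences in treatment effect over separate strata of potentially relevant factors (e.g. gender, baseline BMI, co-morbidities, compliance, etc) will be evaluated", and "A multivariable model will be used to formally establish homogeneity". Section 9.2 then limits the carry-over: "the primary analysis approach will be applied for the quantitative secondairy endpoint parameters". The subgroups that secondary objective 15 plans for every parameter are defined by small bowel length: "To perform analysis of the above parameters in the subgroups with TSBL 500-700 and >700". No analysis of the BMI window by entry BMI is written anywhere in the Protocol.

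**The concern.** A window with two ends behaves differently from a one-sided responder endpoint. More weight loss helps a patient who would otherwise finish above 30 and harms the result of one who would otherwise finish below 22. Which of the two happens depends largely on entry BMI, and eligibility allows a wide range: above 35 with co-morbidity or above 40 without, and not above 50.

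The homogeneity check on %TWL gives no protection here. The effect on %TWL can be exactly 5 points at every entry BMI while the effect on the window changes sign. A pooled table could then be read as no effect on reaching the target BMI, when heavier patients gained and lighter ones overshot. The Protocol itself names too much and too little weight loss as potential risks, and this window is the only BMI-band outcome on its endpoint list.

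**Working it through.** **Inputs from the Protocol.** %TWL has mean 35 and SD 12 in the control arm; the other arm is given as "Experimental group : TWL of 40% (SD 12 or 9"%) (section 7.1.1). %TWL is defined relative to initial weight. There are 92 per arm before drop-out, two-sided alpha 0.05 (section 4.4). Entry BMI runs from 35 to 50 (sections 4.2 and 4.3).

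**Assumptions not in the Protocol.** %TWL is normal, with the same mean at every entry BMI. Entry BMI is normal (42, 4) cut to 35–50. Both are varied below.

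**1. The plan's own figure.** For 35 v 40 with 92 per arm, a noncentral t calculation gives 80.3% power at SD 12/12 and 88.9% at SD 12/9 (Satterthwaite df). The Protocol states 80% and 88.8%, so its inputs are reproduced.

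**2. Window limits at the mean.** Final BMI = b × (1 − TWL/100), with b the entry BMI. At 35% TWL, final BMI exceeds 30 when b > 30/0.65 = 46.2, and falls below 22 when b < 22/0.65 = 33.8. At 40% the limits are 30/0.60 = 50.0 and 22/0.60 = 36.7. These describe a patient exactly at the mean; the spread is added next.

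**3. Probability of the window.** With mean m and SD s,

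P(b) = Φ((100(1 − 22/b) − m)/s) − Φ((100(1 − 30/b) − m)/s).

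- b = 37 (TWL limits 18.9 and 40.5): control Φ(0.46) − Φ(−1.34) = 58.8%; adjusted, SD 12, Φ(0.05) − Φ(−1.76) = 47.8%.
- b = 47 (TWL limits 36.2 and 53.2): control Φ(1.52) − Φ(0.10) = 39.6%; adjusted, SD 12, Φ(1.10) − Φ(−0.32) = 48.9%.

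| Entry BMI | Control | Adjusted, SD 12 | Difference | Adjusted, SD 9 | Difference |
|---|---|---|---|---|---|
| 37 | 58.8% | 47.8% | −10.9 | 51.4% | −7.3 |
| 42 | 55.7% | 56.7% | +0.9 | 69.9% | +14.2 |
| 47 | 39.6% | 48.9% | +9.3 | 59.3% | +19.7 |

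Differences are taken before rounding. The sign changes at entry BMI 41.6 (SD 12/12) or 38.5 (SD 12/9).

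**4. Averages over the assumed entry BMI.** The mix puts 28.6% of patients below 40, 49.6% at 40–45 and 21.8% at 45 or above.

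- SD 12/12: 52.5% v 52.9%. The strata give −8.5, +1.7 and +8.9 points: −8.5 × 0.286 + 1.7 × 0.496 + 8.9 × 0.218 ≈ +0.4. BMI below 22 rises from 16.4% to 27.9%, and BMI above 30 falls from 31.0% to 19.2%.
- SD 12/9: 52.5% v 63.4%. The strata give −2.3, +14.7 and +19.4 points: −2.3 × 0.286 + 14.7 × 0.496 + 19.4 × 0.218 ≈ +10.8 before rounding of the parts.

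**5. Other entry-BMI mixes.** A uniform 35–50 mix gives pooled differences of +0.6 (SD 12/12) and +9.6 (SD 12/9). Truncated normals with mean 40–44 and SD 3–4 give −3.3 to +3.9 and +6.2 to +15.6.

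**6. Mean %TWL rising with entry BMI, in both arms.**

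- SD 12/12: the reversal shrinks but survives a slope of 1.0 point per BMI unit (−3.2 below 40, +3.1 at 45 or above). It is practically gone if %EBMIL is constant (−0.1 and +2.2).
- SD 12/9: the average effect below 40 is about zero at a slope of 0.25 and +2.9 at 0.5. A loss at the lowest entry BMIs lasts to a slope of 0.75 and is gone at 1.0. With constant %EBMIL the effects are about +13 and +15, so there is no reversal.

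**7. Power.** In the step 4 mix, the pooled chi-square test has about 5% power at SD 12/12 and 31% at SD 12/9. The arm × entry-BMI interaction has about 16% and 23%. A two-degree-of-freedom joint test of arm and interaction has only about 12–14% and 39%.

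**The case against.** The unadjusted comparison is valid in a randomised trial, and it answers secondary objective 4, which asks for a comparison of proportions between groups. That stands. It is also why a joint test of arm and interaction should not take its place: such a test can reject when the overall proportions are equal, and at SD 12/12 it would usually miss the pattern anyway.

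A reader might infer that the Protocol's own weight-loss figures force the effect to reverse and cancel. They do not. The Protocol never says that %TWL is unrelated to entry BMI, and step 6 shows that the reversal depends on this. Near-complete cancellation also belongs to 35 v 40 with equal SDs. A smaller SD in the adjusted arm is both a study aim and a stated planning option, and it leaves a visible net gain.

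A reader might also infer that logistic regression is ruled out for this endpoint. The sentence says only that it is not foreseen, and it stands at the end of the side-effects paragraph. The Fisher/chi-square sentence carries the point without it.

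Finally, the quantitative endpoints would probably be examined by baseline BMI, and section 9.3 mentions excessive weight loss among complications. The pattern might therefore be noticed elsewhere. This weakens the point, but neither route shows how the window proportion itself differs by entry BMI.

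**Conclusion.** The point holds in a limited form. The Protocol fixes a pooled test for the BMI window and plans no look at it by entry BMI, while its own planning means allow effects of opposite sign within the eligible range. Under the step 4 assumptions, the base case shows +0.4 points overall with −8.5 below BMI 40 and about +9 at 45 or above. With SD 9 in the adjusted arm, it is about +11 overall with −2 and +19. The size rests on an assumed entry-BMI mix and on %TWL not depending strongly on entry BMI.

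The weakness lies in interpretation: nothing here makes the planned test invalid. Priority is optional to moderate, since this is one of many secondary endpoints and the remedy is cheap.

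**What to change.** In section 9.2, for item 4 only:

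- Keep the comparison of overall proportions. Estimate it as a risk difference standardised over entry BMI, from a logistic model with arm, entry BMI and arm × entry BMI, with a 95% CI. A quadratic term for entry BMI is sensible, because the control probability rises and then falls across the range (52.9% at 35, 60.3% at 39, 29.8% at 50). If the Fisher or chi-square test is kept beside it, state which result carries the conclusion.
- Pre-specify the arm difference with its CI at, for example, entry BMI 37, 42 and 47, as supportive estimates. The interaction term is needed: adjustment for entry BMI alone gives an odds ratio of 1.02 at SD 12/12 (uniform mix) and would not show the reversal.
- State that the closing sentence on logistic modelling does not apply to this endpoint.

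The cost is wording and one more model; entry BMI is already recorded. Because interaction power is low (about 16% at SD 12/12 and 23% at SD 12/9), the estimates by entry BMI should be labelled descriptive, and a non-significant interaction should not be read as homogeneity.

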## Annual safety report

An annual safety report will be made by the investigator and provided to the sponsor.

## Other study parameters

**Safety analysis**

All serious adverse events will be summarized and differences between study groups assessed using the same approach as specified for the quantitative secondary endpoint parameters. Relationship to study intervention, i.e. to the measurement of total small bowel length or adjusting the BP-limb length, will be presented. Furthermore, a differentiation between surgical complications and non-surgical serious complications (e.g. excessive weight loss, diarrhea or nutrient deficiencies) will be provided.

Of all non-serious adverse events only surgical complications will be presented. In this, early (within one month) and late (after one month) surgical complications will be presented separately.

All non-serious, non-surgical complications (e.g. excessive weight loss, diarrhea or nutrient deficiencies) are taken into account as secondary efficacy endpoints.

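### SAE differences are routed to the method for quantitative endpoints, whose Hodges-Lehmann estimate and interval can be exactly zero beside a significant test

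*Protocol*

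**What the plan says.** Three sections of the protocol's statistical chapter form a chain.

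- Safety analysis (under Other study parameters): SAEs are summarised, with "differences between study groups assessed using the same approach as specified for the quantitative secondary endpoint parameters". The section also asks for relationship to the intervention and for a split into surgical and non-surgical serious complications.
- Secondary study parameter(s): "the primary analysis approach will be applied for the quantitative secondairy endpoint parameters".
- Primary study parameter(s): the arms are "compared using two-sample T-test if parameter is normally distributed", with normality judged by "Visual inspection of the distribution, as well as the Shapiro-Wilk test for normality". Otherwise, "If data is skewedly distributed, a Mann-Whitney U-test (Wilcoxon two-sample test) will be applied" and "For the difference in medians, the Hodges-Lehmann estimate will be used with distribution-free 95% confidence intervals".

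The Secondary study parameter(s) section also holds two methods made for event data. One reads "For the qualitative parameters a Fisher exact test or a Chi-square test will be used". The other, for parameters on the occurrence of side effects, reads "estimates of risk differences with 90% confidence intervals, based on the Farrington-Manning Method will be used". The SAE sentence points to neither.

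**The concern.** Whether a patient has an SAE is a yes/no fact, and SAE counts per patient are usually mostly zero. Such data cannot pass a normality check, so the rule ends at Mann-Whitney with Hodges-Lehmann. Hodges-Lehmann is the median of all between-arm pairwise differences. When most pairs are tied at zero, that median is zero whatever the difference in risk.

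The Structured risk analysis says that whether the adjusted limb lengths bring more or fewer adverse events is part of the investigation, and no DSMB is planned. The size of any SAE difference between the arms is therefore a result that readers will look for. An estimate of 0 with an interval of zero width would read as firm evidence of no difference when the data could show the opposite.

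**Working it through.** **The plan's own figures.** The protocol gives no figure for the SAE comparison. The arm size comes from Sample size calculation: difference 5, SD 12, two-sided alpha 0.05 and 80% power give 91.4 by the t-test, hence 92 per arm (power 80.3%), which agrees with the protocol. It then adds 14 to reach 106. The safety set is all randomised patients, so about 106 per arm.

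**Assumptions.** The protocol states neither how SAEs are coded nor an overall SAE rate. I take yes/no per patient and try a range of rates. The only related figure is the 5-10% conversion to RYGB in section 8.2.3.

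**Which branch applies.** Shapiro-Wilk on 0/1 data at 92 or 106 per arm gave p < 1e-13 in every case tried. The t-test branch is closed.

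**When the estimate leaves zero.** With yes/no data each pairwise difference is −1, 0 or 1. The share equal to 1 is p_high × (1 − p_low), and the median becomes 1 only when that share passes 0.5. The higher-risk arm must therefore exceed:

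- 0.5/0.95 = 52.6% if the other arm is at 5%
- 0.5/0.90 = 55.6% if it is at 10%
- 0.5/0.80 = 62.5% if it is at 20%

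**When the interval leaves 0 to 0.** There are 106 × 106 = 11,236 pairs, with the median at 5,618. The distribution-free limits lie at rank 5,618 − 1.96 × √(11,236 × 213/12) = 5,618 − 875 = about 4,743 from either end. The upper limit becomes 1 only when at least about 4,743 pairs equal 1, a share of 0.42.

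**Results at 106 per arm (assumed counts)**

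| SAE patients | Pairs at +1 / −1 / 0 | Hodges-Lehmann (95% CI) | Mann-Whitney p | Fisher p | Risk difference, points (90% score CI) |
|---|---|---|---|---|---|
| 5 v 10 | 1,010 / 480 / 9,746 | 0 (0 to 0) | 0.18 | 0.28 | 4.7 (−1.2 to 11.0) |
| 5 v 20 | 2,020 / 430 / 8,786 | 0 (0 to 0) | 0.0014 | 0.0023 | 14.2 (7.2 to 21.7) |
| 10 v 30 | 2,880 / 760 / 7,596 | 0 (0 to 0) | 0.00046 | 0.00071 | 18.9 (10.3 to 27.6) |
| 10 v 50 | 4,800 / 560 / 5,876 | 0 (0 to 1) | 1.2e-9 | 8.8e-10 | 37.7 (28.3 to 46.7) |

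For 5 v 20, the pairs at +1 are 20 × 101 = 2,020 and those at −1 are 86 × 5 = 430. At 5 v 60, 60 × 101 = 6,060 pairs exceed 5,618 and the estimate jumps to 1, while the risk difference is 55/106 = 51.9 points. Neither value, 0 or 1, describes the difference in risk.

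**Counts instead of yes/no.** In 500 simulated trials with Poisson counts at 106 per arm, the estimate was 0 in 100% at means 0.1 v 0.4 (interval 0 to 0 in 99.6%) and in 96% at 0.1 v 0.6. At 0.2 v 0.9 it was 0 in only 29%. The problem thus carries over to sparse counts and fades as events become frequent.

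**The case against.** The strongest reply is that the rule includes a test as well as an estimate. On 0/1 data Mann-Whitney is almost the chi-square test: for 5 v 20 both give p = 0.0014. The method as written would flag an imbalance about as strongly as Fisher's test. SAEs are also summarised, with the surgical/non-surgical split, so a reader would see the raw imbalance. All of this stands, and it limits the point to the estimate and interval.

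Two stronger readings are tempting, and the documents do not support them. A reader might infer that the safety comparison as a whole would come out as no effect and hide a large excess of SAEs. It would not, because the test and the summaries remain. A reader might also infer that the interval is 0 to 0 whenever most patients have no SAE. At 5 v 50 of 106, most patients in both arms are free of SAEs, yet 50 × 101 = 5,050 pairs equal 1, more than 4,743, and the interval is 0 to 1.

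It can be added that *quantitative* is probably a slip for *qualitative*, and that protection of patients does not rest on this sentence: SAEs are reported individually, and complication reviews start from pooled data with unsealing if rates are high. Both are fair. A slip still needs correcting, because an analyst who follows the text would produce the output shown above.

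**Conclusion.** The point holds, limited to the effect estimate and its interval, and should be fixed. The cross-references are explicit and send SAEs to a method that cannot express a difference in event risk. At 106 per arm it gives 0 with interval 0 to 0 for imbalances such as 5 v 20 or 10 v 30 patients, where the risk differences are 14.2 and 18.9 points. The report would then show a significant p-value beside what looks like a precise absence of difference.

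This rests on two assumptions: yes/no coding per patient (or sparse counts), and SAE rates that the protocol does not supply. Over the yes/no rates tried, the estimate stayed at 0 until the higher arm passed about half of its patients. The primary endpoint, sample size and randomisation are not affected.

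**What to change.** In Safety analysis, refer SAEs to the methods that Secondary study parameter(s) already gives for qualitative and side-effect parameters. For each arm, report the number and percentage of patients with at least one SAE, a Fisher exact or chi-square test, and the Farrington-Manning risk difference with the 90% interval stated there. If the sponsor prefers a 95% interval, it should say why. Keep the existing split into surgical and non-surgical complications.

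Changing *quantitative* to *qualitative* is not enough by itself: it brings in the test but no risk difference. The sentence should also state that the unit is the patient with at least one SAE, which settles the coding.

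The cost is one sentence in the protocol, carried into the SAP if there is one. No data collection or sample size changes. It is best done before the first unblinded comparison, since yearly interim analyses with deblinding are planned from year 1.

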**SUMMARY**

**Rationale:**

Omega-loop gastric bypass (OLGB) surgery aims to reduce weight in obese patients to a healthy BMI. Surgeons usually creat a standard length of the biliopancreatic limb (BP-limb) based on own experience. This practice leads in a substantial percentage of patients to either persisting obesity or underweight. Furthermore, a substantially percentage of patients develop disturbing diarrhea and vitamin and mineral deficiencies. The total small bowel length (TSBL) varies in subjects between less than 5 to more than 10 meters. This variance could have consequences both for weight loss and deficiencies after OLGB. The aim of the study is to investigate whether adjusting the length of the BP-limb tot the TSBL leads to more weight loss with smaller variance and to less bowel movements and less deficiencies of vitamins and minerals using an optimal multivitamin Fitforme WSL primo.

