## Sample size calculation

The null hypothesis in the study is as follows : the percentage TWL at five years in both groups is not different with a mean of 35. The alternative hypothesis is that the mean of the absolute difference in TWL in the experimental group is 5% more than the standard group (40% and 35% respectively).

For the evaluation of the primary endpoint of the percent total weight loss (%TWL) at five years, a sample size of 2x 92 will achieve 80% power to detect a (absolute) difference of -5.0% between the null hypothesis ( both group means of %TWL are 35.0) and the alternative hypothesis (mean of experimental group is a %TWL of 40.0) with estimated group standard deviations of 12.0 and 12.0 and with a significance level (alpha) of 0.05 using a two-sided two-sample t-test.

In case of a reduced standard deviation in the active treatment group of 9.0, the power achieved is 88.8%.

With an expected maximum drop-out due to conversion of OAGB to RYGB of 15% the sample size is 92 plus 14 = 106 patients in each group, leading to a total of 212 participants in the study.

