## Premature termination of the study

Reasons for prematurely termination of the study are :

an unexpectedly high rate of surgical complications due to measuring total small bowel length or adjusting the BP-limb length as to the discretion of the investigator.

An unacceptable percentage of complications like excessive weight loss, diarrhea or nutrient deficiencies in either study arms as to the discretion of the investigator .

This will be investigated, at first without unsealing treatment allocation after the first 50 and 100 operated patients (operative complications) and after 1 and 2 years after start of the study for non-operative complications. If there is a high complications rate in the whole group treatment allocation will be unsealed to investigate further.

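### Non-serious excessive weight loss is left to the secondary endpoints, but the only related endpoint is a pooled BMI 22-30 proportion that cannot separate too much loss from too little

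*Protocol*

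**What the plan says.** In section 9.3 (Safety analysis), serious adverse events are summarised and compared by arm. Serious non-surgical complications are shown apart from surgical ones, and excessive weight loss is given as an example. For the rest, "Of all non-serious adverse events only surgical complications will be presented". The non-surgical remainder is dealt with in one sentence: "All non-serious, non-surgical complications (e.g. excessive weight loss, diarrhea or nutrient deficiencies) are taken into account as secondary efficacy endpoints".

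The weight-related secondary endpoints in sections 2 and 7.1.2 are %TWL, %EWL, %EBMIL and item 4: "Proportion of patients with 22 ≤ BMI ≤ 30 Kg/m^2^ at 1,2,3, 4 and 5 years". Diarrhea corresponds to the bowel-movement endpoints, and deficiencies to items 8 and 9. No item counts patients who lost too much.

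Section 9.2 analyses side-effect parameters by risk difference with a 90% Farrington-Manning interval, without a formal test. Section 7.7 lists among the reasons for stopping "An unacceptable percentage of complications like excessive weight loss, diarrhea or nutrient deficiencies", without defining the first of these. The review at 1 and 2 years is done first without unsealing allocation.

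**The concern.** The protocol treats overshoot as a real outcome. The Summary names underweight as one of the two failures of current practice, the section on risks and benefits lists too much weight loss as a risk, and the Introduction describes a series with 16% of patients below BMI 22. The adjusted arm receives a longer limb than control whenever TSBL is 500 cm or more.

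Nevertheless, non-serious excessive loss is kept out of the adverse-event presentation on the ground that endpoints cover it. %TWL, %EWL and %EBMIL count more loss as more success, with no ceiling. The 22-30 proportion has a lower limit but merges both kinds of failure. If patients move from above 30 to below 22 in similar numbers, the proportion stays flat and no planned summary shows the shift. A reader could see a gain in %TWL and an unchanged range endpoint without learning that more patients had ended below the protocol's own lower limit.

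**Working it through.** **1. The plan's own figure.** Section 4.4 states "a sample size of 2x 92 will achieve 80% power to detect a (absolute) difference of -5.0" percentage points, "with a significance level (alpha) of 0.05 using a two-sided two-sample t-test". With difference 5 and SD 12 in both arms, SE = √((12² + 12²)/92) = 1.769, and the noncentral t gives 80.3% power. With SD 12 and 9, SE = √((12² + 9²)/92) = 1.564 and power is 88.9%. The stated 80% and 88.8% reproduce, so the same means and SDs are used below.

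**2. Inputs.**
- %TWL at 5 years: 35 in control, 40 in the adjusted arm (section 4.4).
- SD: 12 in control; 12 or 9 in the adjusted arm (sections 4.4 and 7.1.1).
- BMI limits 22 and 30 (section 7.1.2, item 4).
- Baseline BMI: the criteria bound it at 35 and 50. No mean or SD is given. **Assumption:** normal, SD 3.5, cut at 35-50, with mean before cutting varied from 38 to 46.
- **Assumption:** %TWL is normal and independent of baseline BMI.

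**3. Formulas.** Final BMI = b × (1 − TWL/100), where b is baseline BMI.
- P(<22) = 1 − Φ((100(1 − 22/b) − mean)/SD)
- P(>30) = Φ((100(1 − 30/b) − mean)/SD)
- P(22-30) is the remainder.

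**4. Worked example at fixed b = 42.** The cut-points in %TWL are 100(1 − 22/42) = 47.6 and 100(1 − 30/42) = 28.6.
- Control 35/12: z = 1.05 and −0.54, giving 14.6% below 22, 29.6% above 30 and 55.7% in the band.
- Adjusted 40/12: z = 0.63 and −0.95, giving 26.3%, 17.0% and 56.7%.
- Adjusted 40/9: z = 0.85 and −1.27, giving 19.9%, 10.2% and 69.9%.

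**5. Averaged over the assumed baseline distribution** (percent; changes are taken before rounding).

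| Baseline mean | <22: control | <22: adjusted SD 12 (change) | <22: adjusted SD 9 (change) | 22-30: control | 22-30: adjusted SD 12 (change) | 22-30: adjusted SD 9 (change) |
|---|---|---|---|---|---|---|
| 38 | 24.7 | 38.7 (+14.1) | 35.6 (+11.0) | 57.2 | 51.5 (−5.8) | 59.1 (+1.9) |
| 40 | 20.5 | 33.4 (+12.9) | 29.2 (+8.6) | 55.8 | 52.9 (−2.9) | 62.3 (+6.5) |
| 42 | 16.3 | 27.8 (+11.5) | 22.5 (+6.2) | 53.0 | 53.4 (+0.4) | 64.2 (+11.2) |
| 44 | 12.6 | 22.6 (+10.1) | 16.7 (+4.1) | 49.3 | 52.8 (+3.5) | 64.1 (+14.8) |
| 46 | 9.8 | 18.6 (+8.8) | 12.3 (+2.5) | 45.2 | 51.3 (+6.0) | 62.3 (+17.1) |

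At mean 42 with SD 12/12, the share above 30 falls from 30.7% to 18.8%. That fall nearly cancels the rise below 22, which is why the band does not move.

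**6. Precision at 92 per arm, mean 42.** With SD 12/12, SE = √(0.163 × 0.837/92 + 0.278 × 0.722/92) = 6.05 points, so the expected 90% interval (Wald approximation) is 11.5 ± 1.645 × 6.05, about +1.6 to +21.5 points. With SD 9 in the adjusted arm it is 6.2 ± 1.645 × 5.81, about −3.3 to +15.8. The separate share would be informative, though not precise.

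**The case against.** Four points can be made in defence.

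- **Serious cases are covered.** A reader might infer that the trial would show no harm at all. The document does not support that: serious excessive weight loss is compared by arm in the SAE summary, and section 7.7 reviews it. This stands, and it confines the point to non-serious cases.
- **The band does take overshoot into account.** Every patient below 22 counts as a failure, and splitting the band could be called tabulation detail for a SAP. The first half is true. The second would hold if the protocol were silent, but section 9.3 bases a reporting exclusion on coverage that the listed endpoints give only in merged form.
- **The size depends on the scenario.** This stands. With SD 9 the band improves at every mean examined and the excess below 22 shrinks to 2.5 points at mean 46. With SD 12 and mean 38, the band falls by 5.8 points and would itself give a warning.
- **The protocol never equates BMI below 22 with excessive weight loss.** This also stands. A reader might want that limit written into the stopping criterion of section 7.7, but that would set a clinical rule and does not follow from this check.

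A reader might also infer that the sample size rests on a smaller SD. It does not: the 92 per arm comes from SD 12 in both arms, and SD 9 appears only as an alternative power figure.

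**Conclusion.** The point holds in a limited form. The statement in section 9.3 that non-serious excessive weight loss is covered by the secondary endpoints is not met by the list in sections 2 and 7.1.2, where the only two-sided weight endpoint merges both directions of failure. Under the protocol's alternative with SD 12/12, the share below BMI 22 rises by about 9 to 14 points while the band changes by about −6 to +6. With SD 9 in the adjusted arm, the rise is about 2.5 to 11 points and the band gains about 2 to 17.

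The existence of the gap rests on the text alone. Its size rests on an assumed baseline BMI distribution and on normal %TWL, so confidence in the size is moderate. The calculation shows that an excess could go unseen; it does not show that the adjusted limb will cause one. A BMI of 22 is used only because it is the protocol's own lower limit.

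**What to change.** 1. In section 7.1.2, item 4, keep the 22-30 proportion and report BMI <22, 22-30 and >30 separately by arm at years 1 to 5.
2. In section 9.2, list the share below 22 among the side-effect parameters, with the risk difference and 90% Farrington-Manning interval already specified there. Treat it as a reporting category, not a clinical threshold.
3. In section 9.3, refer to that analysis by name, so that the statement about coverage becomes true.
4. Reconcile the term excessive weight loss across sections 7.1.2, 7.7 and 9.3. No BMI limit for stopping is proposed here.
5. Optional: the Summary asks whether adjustment "leads to more weight loss with smaller variance", but sections 9.1 and 9.2 consider equality of variance only when choosing the form of the t-test. The SD ratio of 5-year %TWL with a 95% CI could be added as a secondary analysis. A Brown-Forsythe test has about 69 to 70% power for SD 12 versus 9 at 90 per arm (simulation, normal data).

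Cost: weight is already measured at these visits, so no new data, visits or patients are needed. The change is a few sentences and one extra table, plus one short analysis if item 5 is adopted.
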